### Facilitation of the IPB and compliance with the intervention

A facilitation package will be designed to ensure as consistent an approach to facilitation within each intervention Children’s Centre as possible. Discussions will take place between each Fire & Rescue Service local to the four study coordinating centres about the IPB and its implementation. The package will comprise the following:

1. Training session run jointly between the local research team and the Fire & Rescue Service. This will be followed by a meeting run by the same team to design a plan for implementing the IPB in each Children’s Centre and Centres will be expected to provide at least one fire safety session for all parents taking part in the study.
2. One month follow-up telephone contact from the research team to monitor progress and answer any questions;
3. Three month face-to-face meeting between Children’s Centre and research team to monitor progress;
4. Additional meeting at 4-5 months if any Children’s Centre in a study coordinating centre is experiencing difficulties or problems in implementing the IPB;
5. Eight month follow-up telephone contact to monitor progress.

Each contact with a Children’s Centre will be recorded by each research team, together with relevant field notes, on a form and retained within the study notes in each study coordinating centre. Compliance with the intervention will be assessed from the telephone and face to face contacts.

Potential risks and burdens for research participants.

We do not anticipate any potential risks to study participants. The main burden for Children’s Centres will be the time taken to complete questionnaires, undertake the interview and the self-completion tools (see above for details). For family participants, the main obligation will be the time taken to complete the questionnaires (baseline and follow-up). For those families in the IPB with facilitation arm there will also be the time taken to attend between 1 - 5 fire safety sessions at the Children's Centre.

If any participants have suffered a house fire or has had relatives of friends injured in one this may cause distress when parents complete questionnaires. Researchers will be trained to respond sensitively in such situations for example when discussing the study with parents or helping them to complete questionnaires. Specific advice is given in the IPB for Children's Centres about undertaking fire safety sessions in such circumstances.

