The secondary binary outcome measures at family level will be described using frequencies and percentages and compared between treatment arms (I_1_ vs C; I_2_ vs C and I_1_ vs I_2_) using random effects logistic regression to estimate odds ratios and 95% CI, allowing for clustering of responses within Children's Centres. The analyses will adjust for randomisation stratum (study coordinating centre) as a fixed effect and will also adjust for the lead agency of the Children's Centre (Local Authority or NHS led), baseline value of the outcome measure and deprivation (measured using IMD2007 obtained from families’ postcode). The analysis of knowledge scores will be undertaken using random effects linear regression to estimate differences between treatment arms and 95% CI, allowing for clustering of responses within Children's Centres. A residuals analysis will be carried out to check the assumptions of the analysis, and if they are invalid transformations will be considered and if no suitable transformation can be found the score will be dichotomised and analysed using random effects logistic regression. Secondary outcome measures at the level of Children’s centre will be compared using logistic regression if binary and linear regression if continuous, adjusting for randomisation stratum (study coordinating centre) and lead agency of the Children's Centre (Local Authority or NHS led).

A complete case analysis will be undertaken. If any Children’s Centres are lost to follow-up we will consider a range of approaches to undertaking sensitivity analyses to assess the robustness of the findings.

No interim analyses will be undertaken.

Health economic analysis

To assess the cost-effectiveness of implementing an Injury Prevention Briefing in Children’s Centres for preventing fire-related injuries, firstly, resource-use data collected throughout the trial will be combined with unit cost information and summed to obtain an average cost per person (together with its uncertainty) for each intervention. Secondly, these cost data will be combined with the clinical effectiveness data (e.g. proportion of families who have a fire escape plan) to inform the incremental cost-effectiveness analysis. Sensitivity analysis will be undertaken to assess the robustness of the results to any assumptions made in the analysis.

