### Sample size and justification

11 Children’s Centres per arm will allow an absolute difference in the percentage of families with a fire escape plan of 20% in arm I_1_ or arm I_2_ compared to the control arm to be detected. This assumes a control arm prevalence of 42% (obtained from interviews with parents in Children’s Centres in earlier work in the programme of research), 80% power (2-sided 5% significance), an intraclass correlation coefficient of 0.05 (obtained from interviews with parents in Children’s Centres in earlier work in the programme of research) and that outcomes are assessed on 20 families per Children’s Centre. This gives a total of 33 Children’s Centres. In order that all study coordinating centres recruit the same number of Children’s Centres we will recruit a total of 36 Children’s Centres (9 per study coordinating centre), which will also allow for a potential drop-out of one centre per study arm. In order to achieve outcome data on 20 families per Children’s Centre we will aim to recruit 30 families per Children’s Centre; a total of 1080 families.

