### Secondary endpoints

1. The proportion of families with smoke alarms fitted and working on every level will be compared between treatment arms by estimating odds ratios and 95% CI;
2. The proportion of families who report fire-setting or match play by their children will be compared between treatment arms by estimating odds ratios and 95% CI;
3. The proportion of families who have a bedtime routine for preventing fires will be compared between treatment arms by estimating odds ratios and 95% CI;
4. The proportion of families who take part in smoking cessation courses/support will be compared between treatment arms by estimating odds ratios and 95% CI;
5. Scores of knowledge of the causes of fires in the home will be compared between treatment arms using random effects linear regression to estimate a mean difference in score plus 95%CI;
6. The proportion of families satisfied with the home safety information provided by Children’s Centre will be compared between treatment arms by estimating odds ratios and 95% CI;
7. Comparison of families’ resource-use and expenditure in the I_1_ and I_2_ arms incurred as a result of the intervention will be compared using incremental cost effectiveness ratios.

Children’s Centres as participants

1. The proportion of Children’s Centres providing information and advice on the prevention of fire-related injury including fire escape planning, smoke alarms, preventing fire setting or match play, use of bedtime routines for preventing fires, smoking cessation and referral to smoking cessation services. These will be compared between treatment arms by estimating OR and 95% CI.
2. The identification of barriers and facilitators to Children’s Centres implementing the IPB (only in Children’s Centres in the I_1_ and I_2_ arms) (qualitative data analysis);
3. Resource-use and expenditure incurred as a result of the intervention in the I_1_ and I_2_ arms will be compared using incremental cost effectiveness ratios;
4. The success of the process of implementing the IPB in Children’s Centres (using telephone and face-face contact during the intervention period (qualitative data analysis) and the implementation measurement tool that will be developed based on the PARIHS framework)^16^ (quantitative data which will be compared between treatment arms using OR and 95% CI for binary or ordinal data and linear regression for continuous data, if assumptions are met).

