5. The demographic characteristics of participating families compared with those in the catchment area of Children’s Centres using χ^2^ tests and t-tests, or non-parametric tests as appropriate.

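### Two secondary analyses are fixed in a fragile form (minor): ordinary logistic regression on at most 36 centres can separate, and the knowledge score may be switched from a mean difference to a dichotomised odds ratio

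*Protocol*

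**What the plan says.** **Centre-level outcomes.** Protocol, Statistics, Methods: "Secondary outcome measures at the level of Children’s centre will be compared using logistic regression if binary and linear regression if continuous". The same sentence adjusts for study coordinating centre (four strata) and lead agency (two categories), and the Synopsis repeats it. Under Secondary endpoints, the first centre-level item is "The proportion of Children’s Centres providing information and advice on the prevention of fire-related injury", listed over several topics: escape planning, alarms, match play, bedtime routines, smoking cessation and referral. For these the protocol says "These will be compared between treatment arms by estimating OR and 95% CI". Sample size and justification sets 36 centres, nine per coordinating centre, and allows for losing one per arm. No expected rate of advice-giving appears anywhere. In the facilitated arm, "Centres will be expected to provide at least one fire safety session for all parents taking part in the study" (Facilitation of the IPB and compliance with the intervention).

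**Knowledge score.** Methods plans random effects linear regression, and Secondary endpoints promises a mean difference with 95% CI. After a residual check and an attempt at transformation, Methods adds: "if no suitable transformation can be found the score will be dichotomised and analysed using random effects logistic regression". No cut-point is given.

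**The concern.** Logistic regression named without qualification means a maximum-likelihood fit. With few records and several covariates, that fit breaks down when some combination of covariates predicts the outcome perfectly (separation). The simplest case is an arm in which all 12 centres, or none, give advice. The estimated odds ratio for that arm is then infinite, and its Wald interval carries no information. The aim of the intervention pushes this outcome towards its ceiling, so success in I1 is the very situation in which the planned analysis can fail. A replacement would then have to be chosen after the data are seen.

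For the knowledge score, the concern is that a diagnostic on the outcome data decides what is estimated. If the fallback is reached, the reader gets an odds ratio on a split score in place of the mean difference, with less power.

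**Working it through.** **The plan's own figure.** The protocol gives no figure for either analysis. Its only sample size is for the primary outcome, and it reproduces. For 42% versus 62%, two-sided 5%, 80% power, with continuity correction, n = 107 per arm before clustering. The design effect is 1 + (20 − 1) × 0.05 = 1.95. Then 107 × 1.95 / 20 = 10.43, so 11 centres per arm, as stated.

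**Part 1, inputs.** From the protocol: 36 centres, four strata of nine, three arms, hence 3 centres per arm per stratum and 12 per arm. Parameters: intercept 1 + arm 2 + stratum 3 + lead agency 1 = 7. Assumed: the provision rates, and 50–75% of centres under one lead agency.

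*Chance that all 12 centres in an arm provide advice*, p^12:

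| p | p^12 |
|---|---|
| 0.50 | 0.0002 |
| 0.70 | 0.014 |
| 0.80 | 0.069 |
| 0.85 | 0.142 |
| 0.90 | 0.282 |
| 0.95 | 0.540 |

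*Chance that at least one arm is full*, 1 − (1 − p_C^12)(1 − p_I2^12)(1 − p_I1^12); the chance of an empty arm is negligible here:

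- 50/70/80%: 1 − 0.9998 × 0.986 × 0.931 = 0.08
- 50/85/85%: 1 − 0.9998 × 0.858² = 0.26
- 50/70/90%: 1 − 0.9998 × 0.986 × 0.718 = 0.29
- 80/95/95%: 1 − 0.931 × 0.460² = 0.80

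*Simulation of the full seven-parameter model*, with a linear-programming check for a separating direction. Ranges span separate simulations:

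| Provision C/I2/I1 (assumed) | Separation anywhere | Arm odds ratio infinite |
|---|---|---|
| 50/50/50% | about 2% (2–3%) | roughly 0% |
| 50/70/80% | 14–19% | 6–11% |
| 50/85/85% or 50/70/90% | 36–41% | 25–31% |
| 80/95/95% | over 90% | about 80% |

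The last column agrees with the binomial arithmetic. The two columns differ because separation can lie in a stratum or lead-agency term and leave the arm contrast estimable. With a 90:10 lead-agency split and 50% provision everywhere, for example, separation rises to 29%, yet an arm is full or empty in only 0.1% of runs.

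**Part 2.** For a normally distributed score split so that a fraction c falls on one side, the share of information kept is φ(z_c)² / [c(1 − c)]. An analysis with 80% power then has power Φ[(1.960 + 0.842) × √share − 1.960].

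- Median split: 0.399² / 0.25 = 0.637. Power = Φ(2.802 × 0.798 − 1.960) = Φ(0.276) = 61%.
- 80/20 split: 0.280² / 0.16 = 0.490. Power = Φ(2.802 × 0.700 − 1.960) = Φ(0.001) = 50%.

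These figures are illustrations. The fallback applies when the model assumptions have failed, and the loss for a non-normal score will differ.

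On whether a mean difference remains usable: 12 × 20 = 240 families per arm. If the protocol's ICC of 0.05, which was obtained for the primary outcome, also held for the score, that is 240 / 1.95 = 123 effective families in 12 clusters per arm. The mean difference does not require normal residuals, but its interval must respect centres and their small number.

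**The case against.** The case against has real weight. The protocol says a separate analysis plan will be written, and fallbacks for sparse data and cut-points commonly belong there. Logistic regression with the centre as the unit is the right class of model, adjusted for the stratification factor. One expected fire safety session does not mean that every centre covers match play, bedtime routines or referral to smoking cessation, so full provision on every topic cannot be assumed. Dichotomising is the third step, after a failed check and failed transformation, and the trigger is wider than non-normality.

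This limits the point but does not remove it. The protocol states the estimator and the fallback; it does not leave them open. For both there is a better choice at no cost in data.

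Three stronger readings are tempting, and the documents support none of them.

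- *That the centre-level odds ratios will usually not exist.* Without provision rates this cannot be derived; at 50% in every arm separation is rare.
- *That the protocol contradicts itself on the knowledge score.* A conditional fallback does not contradict the main analysis promised under Secondary endpoints.
- *That the comparison of participating families with the catchment ("χ^2^ tests and t-tests, or non-parametric tests as appropriate") is miscalibrated because it ignores centre.* The comparison is descriptive and no treatment effect depends on it. The text does not say that data are pooled across centres. The size, and even the direction, of any error depends on assumed catchment sizes and between-centre variation.

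**Conclusion.** Both parts hold as minor points on secondary outcomes; the primary analysis is untouched.

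Part 1 carries more weight. The planned fit can separate, and it does so often if provision is near the ceiling that the facilitation package aims for. The arm odds ratio is infinite in anything from almost no trials to about 80%, depending wholly on provision rates that the protocol does not give. The range also rests on an assumed lead-agency split and on all 36 centres being retained.

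Part 2 matters only if the last-resort step is reached. It then changes the quantity estimated on the strength of the outcome data. A median split of a normal score would keep 64% of the information; for the score actually observed the loss is unknown.

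**What to change.** **Centre-level binary outcomes.** Specify Firth-penalised logistic regression with profile-likelihood intervals, or exact logistic regression, keeping the same covariates, and report the counts per arm alongside. The price is slight shrinkage of the odds ratio. Intervals will still be wide, since no method adds information to 12 centres per arm.

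**Knowledge score.** Delete the dichotomisation step. Keep the adjusted mean difference as the estimate in all cases. If the model assumptions fail, take its interval from a bootstrap that resamples centres, or from a cluster-robust variance with a small-sample correction.

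Both changes are wording in the protocol or analysis plan and use standard software. They need no extra data and should be made before anyone sees outcomes by arm.

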### Sample size and justification

11 Children’s Centres per arm will allow an absolute difference in the percentage of families with a fire escape plan of 20% in arm I_1_ or arm I_2_ compared to the control arm to be detected. This assumes a control arm prevalence of 42% (obtained from interviews with parents in Children’s Centres in earlier work in the programme of research), 80% power (2-sided 5% significance), an intraclass correlation coefficient of 0.05 (obtained from interviews with parents in Children’s Centres in earlier work in the programme of research) and that outcomes are assessed on 20 families per Children’s Centre. This gives a total of 33 Children’s Centres. In order that all study coordinating centres recruit the same number of Children’s Centres we will recruit a total of 36 Children’s Centres (9 per study coordinating centre), which will also allow for a potential drop-out of one centre per study arm. In order to achieve outcome data on 20 families per Children’s Centre we will aim to recruit 30 families per Children’s Centre; a total of 1080 families.

# Qualitative data

Data from the interviews with Children’s Centre managers and staff will be managed using a qualitative data management package e.g. QSR NVIVO. The transcripts will be read and re-read to identify themes emerging on the barriers and facilitators and implications for practice and these will be documented. Framework Analysis^19^ will be used. The initial framework will be developed and agreed by researchers from the 4 centres and lay research advisors using data from 8 interviews representing a range of Children’s Centres. This framework will be used by a researcher based in Bristol to undertake the analysis of the rest of the interviews. The framework and analysis will be independently checked in Nottingham and the final framework agreed for analysis of the remaining data. The findings will be reported using anonymised quotations. Data from the telephone contacts and face-face contacts between Children’s Centres and researchers will be analysed manually using content analysis after categorisation into main sub-headings^20, 21^. A thematic analysis will then be conducted.

### Assessment of efficacy

Unless stated otherwise, all comparisons will be made between I_1_ vs C; I_2_ vs C and I_1_ vs I_2_ arms.

### Primary endpoint

Family participants

The proportion of families who have a fire escape plan will be compared between treatment arms by estimating odds ratios and 95% CI.

### Secondary endpoints

1. The proportion of families with smoke alarms fitted and working on every level will be compared between treatment arms by estimating odds ratios and 95% CI;
2. The proportion of families who report fire-setting or match play by their children will be compared between treatment arms by estimating odds ratios and 95% CI;
3. The proportion of families who have a bedtime routine for preventing fires will be compared between treatment arms by estimating odds ratios and 95% CI;
4. The proportion of families who take part in smoking cessation courses/support will be compared between treatment arms by estimating odds ratios and 95% CI;
5. Scores of knowledge of the causes of fires in the home will be compared between treatment arms using random effects linear regression to estimate a mean difference in score plus 95%CI;
6. The proportion of families satisfied with the home safety information provided by Children’s Centre will be compared between treatment arms by estimating odds ratios and 95% CI;
7. Comparison of families’ resource-use and expenditure in the I_1_ and I_2_ arms incurred as a result of the intervention will be compared using incremental cost effectiveness ratios.

Children’s Centres as participants

1. The proportion of Children’s Centres providing information and advice on the prevention of fire-related injury including fire escape planning, smoke alarms, preventing fire setting or match play, use of bedtime routines for preventing fires, smoking cessation and referral to smoking cessation services. These will be compared between treatment arms by estimating OR and 95% CI.
2. The identification of barriers and facilitators to Children’s Centres implementing the IPB (only in Children’s Centres in the I_1_ and I_2_ arms) (qualitative data analysis);
3. Resource-use and expenditure incurred as a result of the intervention in the I_1_ and I_2_ arms will be compared using incremental cost effectiveness ratios;
4. The success of the process of implementing the IPB in Children’s Centres (using telephone and face-face contact during the intervention period (qualitative data analysis) and the implementation measurement tool that will be developed based on the PARIHS framework)^16^ (quantitative data which will be compared between treatment arms using OR and 95% CI for binary or ordinal data and linear regression for continuous data, if assumptions are met).
5. The demographic characteristics of participating families compared with those in the catchment area of Children’s Centres using χ^2^ tests and t-tests, or non-parametric tests as appropriate.

### Assessment of safety

No adverse events are anticipated. Should an adverse event occur the Chief Investigator will be informed who will also report this to the TSC.

### Procedures for missing, unused and spurious data

A complete case analysis will be undertaken. If any Children’s Centres are lost to follow-up we will consider a range of approaches to undertaking sensitivity analyses to assess the robustness of the findings.

### Definition of populations analysed

Full Analysis: the full analysis set will be all families on whom a follow up assessment of the primary outcome measure is available. Every effort will be made to keep in contact with families, even if they move house to an area covered by a different Children’s Centre, to minimise losses to follow-up.

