2. A member of the Children’s Centre staff will give parents attending the Centre a study invitation letter, participant information sheet (PIS), baseline questionnaire and a consent form. Parents will have the study explained to them and will be given the opportunity to discuss the study and ask any questions they would like to prior to completing and returning the consent form. This may be in person with the researcher at an arranged time or by telephone;
3. A member of the Children’s Centre staff will approach parents in the Children’s Centre. Parents will have the study explained to them and be given a study invitation letter, participant information sheet (PIS), baseline questionnaire and a consent form. Parents will be given the opportunity to discuss the study with the researcher who will be present within the Children’s Centre and ask any questions they would like to prior to completing and returning the consent form. Where participants are happy to complete the consent form at this point, parents will be invited to complete the questionnaire whilst the researcher and Children’s Centre staff are present. If they do not wish to do this they will be provided with a freepost envelope to return the consent form and completed questionnaire.

If needed, the usual Children’s Centre interpreter and translator services will be available to assist with discussion of the trial, the participant information sheets and consent forms. The consent forms and information sheets will not be available printed in other languages. Participants will only be considered to be recruited to the trial if they complete a consent form and the baseline questionnaire.

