**ANALYSES**

# Statistics

### Methods

An analysis plan will be produced by the trial statistician and health economist, who will oversee and/or undertake the statistical and economic analyses.

All analyses will be conducted on an intention-to-treat basis in that families and Children’s Centre managers and staff will be analysed in the group to which they were randomised, regardless of the intervention actually received (eg. if the family moved and used a different Children’s Centre). Analyses will conform to a pre-specified analysis plan and will be undertaken blind to treatment arm allocation.

Characteristics of Children’s Centres and families at baseline will be compared informally between the three treatment arms. The primary outcome measure (having a fire escape plan at 12 months) will be described using frequencies and percentages and compared between treatment arms (I_1_ vs C; I_2_ vs C and I_1_ vs I_2_) using random effects logistic regression to estimate odds ratios and 95% CI. This analysis will have families at level one and Children’s Centres at level two, to allow for clustering of responses within Children's Centres. The primary analysis will adjust for randomisation stratum (study coordinating centre) as a fixed effect and will also adjust for the lead agency of the Children's Centre (Local Authority or NHS led), having a fire escape plan at baseline and deprivation (measured using IMD2007 obtained from families’ postcode). Deprivation has been specified as it is strongly associated with house fire injuries^2,3^ and measures of deprivation have previously been found to be associated with the effectiveness of home injury prevention interventions^18^.

The ICC and 95% CI will be estimated for the primary outcome measure from the regression models. Models will be checked by examining level 2 residuals for normality and constant variance and level 1 and level 2 residuals for outliers.

Sub-group analyses will explore differential effects by deprivation, measured using the IMD2007, by adding interaction terms to the regression model for the primary outcome measure. IMD will be entered as a continuous covariate if there is a linear relationship with outcome.

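### The full analysis set is defined by the primary outcome alone, but the complete-case rule could drop some of its families from the adjusted primary model because a baseline covariate is missing.

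*Protocol*

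**What the plan says.** Under Definition of populations analysed, the protocol gives a single set: "the full analysis set will be all families on whom a follow up assessment of the primary outcome measure is available". No set is given for any other outcome.

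Under Procedures for missing, unused and spurious data it says "A complete case analysis will be undertaken". The same rule appears in the Synopsis and at the end of the statistical Methods. None of these places says whether complete means complete on the outcome or on the outcome and all covariates. The only further step concerns whole clusters: "If any Children’s Centres are lost to follow-up we will consider a range of approaches to undertaking sensitivity analyses".

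Under Methods, "The primary analysis will adjust for randomisation stratum (study coordinating centre) as a fixed effect". The model also adjusts for lead agency and for "having a fire escape plan at baseline and deprivation", with deprivation taken as IMD2007 from the family's postcode. The secondary binary models at family level use the baseline value of their own outcome, plus IMD2007.

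Under Recruitment, "Participants will only be considered to be recruited to the trial if they complete a consent form and the baseline questionnaire".

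**The concern.** Stratum and lead agency are properties of the Centre and should be known for every family. The baseline plan item and IMD2007 are family-level and can be missing for an individual family. The usual reading of complete case in a regression is that a record lacking any model variable is left out. On that reading, a family that gave the primary outcome at follow-up but left the baseline plan item blank, or whose postcode cannot be matched to an IMD score, is in the full analysis set but not in the primary model. Two stated rules then give two different populations for the same analysis.

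What is at stake is mainly precision and clarity. Families with an observed primary outcome would be set aside because of a gap in a covariate fixed before randomisation. Each secondary model, with its own baseline item, would also have its own population.

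A smaller ambiguity lies alongside. Because the only set is conditioned on the primary outcome, a reader could take it to govern the family-level secondary outcomes too.

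**Working it through.** **1. Passages side by side.** Take a family with the follow-up plan item answered and the baseline plan item blank.
- Definition of populations analysed: included, since only the follow-up primary outcome is required.
- Complete-case rule applied to the model in Methods: excluded, since a model variable is missing.
- Sensitivity analyses: not triggered, since they are foreseen only when a Centre is lost.

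The two populations coincide only if both family-level covariates are complete.

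**2. The plan's own sample size.** Inputs from Sample size and justification: 42% v 62%, two-sided 5%, 80% power, ICC 0.05, 20 families per Centre.
- Two-proportion formula with continuity correction: 107 families per arm before clustering.
- Design effect: 1 + (20 − 1) × 0.05 = 1.95.
- Centres per arm: 107 × 1.95 / 20 = 10.43, rounded up to 11.

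The stated 11 per arm is reproduced. Without the continuity correction the result is 97 × 1.95 / 20 = 9.46, rounded up to 10.

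**3. Power if covariate gaps remove families.** The protocol gives no rate of missing covariates, so a range is assumed. With k Centres per arm and m usable families per Centre, the effective number per arm is n = k·m / [1 + (m − 1) × 0.05]. Power is Φ(0.20 / √[(0.42 × 0.58 + 0.62 × 0.38) / n] − 1.96), where the bracketed sum is 0.2436 + 0.2356 = 0.4792. The last two columns use the pooled variance under the null instead. No column has a continuity correction.

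| Assumed missing | m | n (k = 11) | Unpooled, k = 11 | Pooled, k = 11 | Pooled, k = 12 |
|---|---|---|---|---|---|
| 0% | 20 | 112.8 | 86.6% | 85.7% | 88.6% |
| 5% | 19 | 110.0 | 85.8% | 84.8% | 87.8% |
| 10% | 18 | 107.0 | 84.8% | 83.9% | 86.9% |
| 20% | 16 | 100.6 | 82.6% | 81.5% | 84.8% |

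At 30% missing (m = 14) the pooled figures are 78.5% with 11 Centres per arm and 82.0% with 12. The loss is damped because the design effect shrinks with m: at m = 16 it is 1.75, so losing 20% of families costs about 11% of the effective number (100.6 / 112.8 = 0.89).

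**4. Timing of the covariates.** Under Randomisation and blinding, a Centre is allocated only after its families have been recruited, and recruitment requires the baseline questionnaire. Whether a baseline item is blank therefore cannot depend on the arm. This is why a simple fill-in is acceptable for these covariates in a randomised comparison.

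**The case against.** The strongest reply is that the gap may hardly arise. A family is not recruited without a completed baseline questionnaire, families must live in the Centre's catchment and their addresses are stored, and questionnaire entries are verified by inspection. All of this stands and limits the problem to residual item non-response and unusable postcodes. It does not remove the problem: a questionnaire can be returned and accepted with an item left blank.

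The second reply is that handling of missing covariates and the denominator for each outcome usually belong in the analysis plan, which the protocol announces and which is not at hand. That would dispose of a mere omission. Here, however, the protocol states a rule, complete case, and that rule read in the usual way shrinks the set it defines. A plan that kept these families would need the rule clarified first.

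Two stronger readings are tempting and should not be drawn. One is that usable secondary data are discarded. No sentence says that the full analysis set governs secondary outcomes, Methods describes the secondary models without mentioning it, and Centre-level outcomes could not be governed by a set of families. Even a literal reading would lose only families who returned the follow-up questionnaire with the primary item blank. The other is that intention-to-treat is contradicted. The protocol uses that term for analysis in the group as randomised, whatever intervention was received. It makes no promise about missing data, and a complete-case analysis by allocated arm is consistent with it.

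**Conclusion.** The point holds as a minor, conditional inconsistency. If any family with a follow-up primary outcome lacks the baseline plan item or a usable postcode, the adjusted primary model will be run on fewer families than the stated full analysis set. Under an assumed 5% to 20% missing, power with 11 Centres per arm falls from about 86-87% to about 82-86%, depending on the variance formula. It stays above 80%, and is higher with the 12 Centres per arm to be recruited. The sample size needs no change. No bias in the comparison is shown, and none should be inferred from these figures. The size rests entirely on the assumed rate of missing covariates, which the protocol does not give.

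**What to change.** In Procedures for missing, unused and spurious data (and where the rule is repeated in the Synopsis and Methods), state that complete case refers to the outcome only. Families with a missing pre-randomisation covariate are kept, with a missing-category indicator for the baseline item and the Centre mean, or a similarly simple value, for IMD2007 in the main-effect models. The planned interaction analysis by deprivation should use observed IMD only, because there a Centre mean would stand in for the family-level deprivation under study.

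In Definition of populations analysed, add that each family-level secondary outcome is analysed in all randomised families who have that outcome at follow-up.

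The cost is a few sentences and slightly more analysis work, with an approximate covariate value for a few families. No new data are needed.
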